## Data analysis

### Quantitative data analysis

We will do statistical analysis, for example variance analysis with repeated measurement and chi-square tests to evaluate following hypotheses:
a)Main outcome: In regard of the development of school attendance and school related symptoms during treatment: The overall symptoms (SDQ) and the school related symptoms (SEQ-SS, ISV) will improve significantly from the beginning of the rehabilitation project to the end of the treatment (SDQ, ISV: T1 > T2; SEQ-SS: T1 < T2). At least 75% of the participants show a regular school attendance, defined as <10% of absenteeism in school weeks during the period T2—four weeks. The global functioning in daily life improves significantly from beginning to end of treatment (HoNOS-CA: T1 > T2).b)Follow-up assessment: In regard of the development of school attendance and school-related symptoms after the treatment: The overall symptoms and the school-related symptoms will stabilize or improve in the 6 months following the end of treatment (SDQ, ISV: T2 ≥T3, SEQ-SS: T2 ≤ T3). At least 75% of the participants achieve the proximal school goal and at least 75% of the participants show a regular school attendance, defined as <10% absenteeism during the period T3—four weeks. The global functioning in daily life is maintained or improved in the six-month following the end of treatment (HoNOS-CA: T2 ≥ T3).Data analyses will be performed with SPSS software.

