### Objective

The aim of this article is to present the study protocol for the evaluation of the described model project. On the one hand the evaluation study has a summative concern, by getting information whether the treatment can improve school attendance, reduce clinical symptoms and enhance participation of young people (main outcome) and whether these effects can be maintained in the long term (follow-up assessment).

The hypotheses are:
1.At the end of treatment psychiatric and school-related symptoms (e.g., anxiety, depression, problems with peers at school, problems with teachers) will improve, school attendance increases, and global functioning in daily live will improve, too.2.The improvement could be maintained or even augmented in the following six months.To this end, data on symptoms, school attendance and global functioning will be collected at three points in time: at the beginning of treatment, at the end of treatment and six months after the end of treatment. On the other hand, the formative evaluation aims to explore the acceptance of the treatment by the treated families, the treatment team and stakeholders. For this purpose, data will be collected from stakeholders and interviews will be conducted with children, adolescents, and their parents.

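### The six-month stability hypothesis is paired with difference tests that cannot establish stability, and the T3 attendance criterion takes no account of T2 status

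*Protocol article*

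**What the plan says.** Under Objective, the second hypothesis of the protocol article reads: "The improvement could be maintained or even augmented in the following six months". Quantitative data analysis turns this into hypothesis set (b):

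- **Symptoms and self-efficacy.** They "will stabilize or improve in the 6 months following the end of treatment", written as T2 ≥ T3 for SDQ and ISV and T2 ≤ T3 for SEQ-SS. Equality counts as success.
- **Functioning.** It is to be kept up or improved, again as T2 ≥ T3 on HoNOS-CA.
- **Attendance.** The criterion is that "at least 75% of the participants show a regular school attendance, defined as <10% absenteeism during the period T3—four weeks". The same 75% level applies at T2, and no T2-to-T3 comparison is stated.

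One sentence introduces the methods for both hypothesis sets: "We will do statistical analysis, for example variance analysis with repeated measurement and chi-square tests to evaluate following hypotheses". Set (a), T1 to T2, asks for significant improvement in symptoms and functioning. Set (b) does not use the word significant and does not say what counts as stable.

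**The concern.** Set (a) is a claim of change, and a difference test suits it. Set (b) is a claim that nothing got materially worse. A difference test can reject no change in either direction, but failing to reject is not evidence of stability, and it becomes more likely as fewer participants reach T3. If the named methods are carried over to set (b), weaker data make the favourable reading easier to obtain.

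The attendance criterion has a different problem. Hypothesis 2 is about keeping what was gained, but a fixed level at T3 shows neither how far attendance fell after T2 nor who relapsed. Keeping young people in school over time is part of the programme's stated objective, and the abstract describes the condition as prone to relapse. The trial's conclusion about durability therefore rests on this part of the plan.

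**Working it through.** **Inputs.** From the article: N = 162 (Sample size and randomization), the inequalities of set (b), and the 75% level. N = 162 comes from expected patient numbers, so there is no power figure for T2 to T3 to reproduce. Assumed here because the article gives no values: two-sided alpha of 0.05, a paired comparison, effects in SDs of the T2-to-T3 change, and completer numbers of 130 and 100 as examples of loss.

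**1. A difference test applied to a stability claim.** The largest observed worsening that stays non-significant is t(0.975, n−1)/√n: 1.975/√162 = 0.155 SD at n = 162, and 1.984/√100 = 0.198 SD at n = 100. The probability that a true worsening is non-significant (noncentral t) is:

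| True worsening | n = 162 | n = 130 | n = 100 |
|---|---|---|---|
| 0.15 SD | 53% | 60% | 68% |
| 0.20 SD | 28% | 38% | 49% |

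**2. Two possible readings of T2 ≥ T3 at n = 162.** Read literally on observed means, a true worsening of 0.20 SD passes with probability Φ(−0.20 × √162) = Φ(−2.55), about 0.5%. A truly stable scale then passes only half the time. Read as no significant difference, the same worsening passes 28% of the time. The two readings give very different verdicts.

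**3. The 75% level, net change.** With 162 assessed, 0.75 × 162 = 121.5, so 122 regular attenders (75.3%) meet the criterion. The largest net fall that still meets it is:

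| Regular at T2 | Net loss allowed | Points |
|---|---|---|
| 162 (100%) | 40 | 24.7 |
| 154 (95%) | 32 | 19.8 |
| 146 (90%) | 24 | 14.8 |
| 138 (85%) | 16 | 9.9 |
| 130 (80%) | 8 | 4.9 |

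The fall from 154 to 122 is far from chance: exact McNemar p is about 0.000009 even if 10 participants move the other way (42 losses, 10 gains).

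**4. The 75% level, individual relapse.** The criterion allows 162 − 122 = 40 irregular attenders at T3, and it does not ask whether they were regular at T2. With 122 regular at T2, 40 of them (40/122 = 33%) could relapse while the other 40 become regular. T3 is again 122 and the criterion is met with no net change.

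**5. Is a margin-based reading feasible?** With no true change and a one-sided 2.5% limit, power is about Φ(m√n − 1.96).

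- m = 0.25, n = 162: Φ(3.18 − 1.96) = 89%.
- m = 0.25, n = 130: Φ(2.85 − 1.96) = 81%.
- m = 0.20: 80% power needs ((1.96 + 0.842)/0.20)² ≈ 197 completers, more than the planned 162.

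Under m = 0.25, a true worsening of 0.20 SD is accepted with probability Φ(0.05√n − 1.96): Φ(−1.32) = 9% at n = 162 and Φ(−1.46) = 7% at n = 100. Losing participants no longer helps the claim.

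**The case against.** The strongest reply is that the article contains no faulty decision rule. The tests are introduced with "for example variance analysis with repeated measurement and chi-square tests", so the list is open. No sentence equates a non-significant T2-to-T3 result with stability. Read literally, T2 ≥ T3 is contradicted by any observed mean worsening. Margins and confidence-interval rules are often left to an analysis plan, which is not shown here. For attendance, 75% is an absolute target at both times, so a fall from 95% to 75% would be visible in the planned results. If T2 is close to 75%, no net fall can be hidden. The follow-up is kept separate from the main outcome, and the Discussion calls the evaluation explorative.

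Most of this stands, and it limits the point. A reader might infer that a non-significant worsening or a large relapse would be reported as maintained benefit. The document does not support that; it only leaves the outcome possible. The absence of a margin from a journal article is also not a fault in itself. What remains is fixed in the published text: a stability hypothesis coupled to difference-type methods, and a T3 attendance criterion with no link to T2. The literal reading does not rescue the plan either, since it would fail a truly stable scale half the time. Showing both proportions would reveal a net fall, but not individual relapse offset by new attenders.

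**Conclusion.** The point holds in limited form. As published, set (b) could let a modest worsening on a scale pass as stable: 28% for a true 0.20 SD at n = 162, and 49% at an assumed 100 completers. These figures rest on an assumed paired two-sided 5% test and on non-significance being read as stability, which the article does not state.

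The attendance criterion tolerates a net fall of about 20 points from a T2 level of 95%, and at most about 25 points from 100%. The room shrinks to nothing as T2 approaches 75%. Offsetting individual relapse can be hidden even when T2 is at 75%. A reader might also take the criterion as the article's declared proof of maintenance. It is given only as a T3 target, so the criticism is that it does not answer hypothesis 2, not that the article claims it does.

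This should be put right before T3 data are examined. It concerns the follow-up conclusion, not the T1-to-T2 main outcome.

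**What to change.** For SDQ, ISV, SEQ-SS and HoNOS-CA, estimate the paired mean change from T2 to T3 with a 95% CI. Conclude that the gain was maintained only if the interval excludes a worsening larger than a margin that the sponsor justifies before T3 data are seen. The 0.25 SD used above is an illustration; nothing in the article supports a particular value, and 0.20 SD would be out of reach at 80% power with 162 participants.

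For attendance, keep the 75% target and add two results: the paired T3-T2 difference in the proportion regular, with a 95% CI, and the proportion of T2 regular attenders still regular at T3. With 162 pairs, the CI half-width is about 1.96 × √(d/162), where d is the assumed share of participants who change status: 4.9, 6.9 and 8.4 points for d = 10%, 20% and 30%. Conditioning on T2 regular attenders is preferable to requiring regular attendance at both times, because the latter mixes success at T2 with maintenance and counts late improvers as failures.

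The cost is wording only, since T2 and T3 data are already collected under participant codes. The price for the sponsor is committing to a margin in advance and accepting a stricter standard for claiming maintenance.

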### Qualitative data analyses

For the formative evaluation, we will need self-designed surveys, which ask for the formative evaluation. They will be evaluated using summative scores and cluster analyses.

The interviews are based on a semi structured guide: there are predefined questions that can be explored in more depth interactively during the interview. The questions relate to the decision to participate in the program, which treatment components were offered and participated in, whether these were helpful, and how the cooperation within the treatment team or between stakeholders was perceived. In addition, participants are asked whether their goals were achieved and what exactly helped them to achieve these goals. Finally, participants are asked to summarize their satisfaction with the treatment. The interviews are conducted by trained researchers and then transcribed verbatim.

The analysis of the interviews will use focused analysis of qualitative interviews (45). In this technique, relevant categories are identified through intensive reading of transcripts interviews, summarizing passages and abstracting, then building codes that are fine-tuned by applying them to transcripts of further interviews. The generated codes then are used to find hypotheses about several formative evaluation questions, e.g., do the parents and adolescents think that the rehabilitation project is helpful, which aspects are important for their opinion, which aspects are important for acceptance of the treatment, which aspects are likely to cause a premature end? Then the interrelationship between the results of the quantitative and the qualitative analyses will be discussed.

## Discussion

Because of the continuing high number of children and young people with mental illnesses (18, 19) and the associated fractures in their educational biographies with long-term effects (1, 4), there is an urgent need to improve existing treatments and develop new approaches (1, 12). This is the concern of the described rehabilitation project. The individual and societal costs of low educational attainment, chronic absenteeism and avoidance are long-lasting and high (6, 10). In Germany, the social security system with health, long-term care, unemployment and pension insurance funds the treatment of these restrictions. However, this implies that these systems should work as efficiently as possible. Therefore, a scientific evaluation of all community-financed interventions is of high interest. This study aims to contribute to this.

Previous research on existing treatment for children and adolescents with EBSA shows that there are many helpful approaches especially for the treatment of mental illness (23–28). However, focusing on sustainable school reintegration and promoting participation in all areas of daily life is still little widespread (46). If the scientific evaluation shows that SchuTIng-stAR is an appropriate intervention, which is acceptable to families and has an impact on school attendance and mental health, this may help to ensure that the offer is continued and possibly extended to other clinics.

However, there are limitations to the systematically derivation of causal effects due to the research design. First, there is no control group. This was decided in order to ensure that as many children and adolescents as possible could participate in the rehabilitation project.

Second, the intervention is a completely new form of treatment. We hope to minimize the need for adapting the treatment during the study period by piloting first. But there still might emerge some aspects which leads to adoption or sharpening of interventions during the trial period, what will be documented thoroughly. This also limits the value of the data to be extracted.

Nevertheless, it seems reasonable and worthwhile to evaluate this intervention in this explorative way in order to gain insight into outcome trends relevant factors. The mixed-methods design with interview data and qualitative analysis methods also addresses the need to gain insights in a treatment setting that is as natural as possible. In this way, we can learn about not only the reduction of school absenteeism, but also about what makes it easier for children, adolescents and families to participate in such an intervention, and what leads to treatment refusal, dropout or lack of success.

We are confident that the study, despite its methodological limitations, can make a valuable contribution to understanding the difficulties that mentally ill children and adolescents have in attending school. So wecan provide insights into the needs of support in the systems involved (family, school, youth welfare) to cooperate with each other in the best interests of the young people and to help to design effective treatment approaches.
